### 2.5. Voice recording protocol

Voice recordings will be obtained using a Jabra Speak 510 USB omnidirectional microphone, positioned frontally at a distance of no more than 20 cm from the participant’s mouth. Recordings will be conducted in a quiet hospital room, with minimized background noise, closed doors and windows whenever feasible, silenced electronic devices, and no overlapping speech or external interruptions whenever possible.

The Jabra Speak 510 microphone was selected for pragmatic and translational reasons: it is affordable, widely available, easy to deploy and compatible with routine hospital use. This choice prioritizes ecological validity over laboratory-grade audio fidelity, which may reduce the precision of signal-sensitive measures such as jitter, shimmer, HNR, and intensity. This potential variability will be reduced by maintaining the same microphone, configuration, placement, and recording conditions throughout the study. This approach is consistent with previous studies that have used non-specialized recording devices, including tablet microphones, smartphone microphones and mobile phones, to extract clinically relevant speech and voice features [19,24,25,30].

Repeated assessments will be scheduled within a similar time-of-day window for each participant whenever feasible. Because recordings are integrated into routine clinical visits, exact consistency cannot be guaranteed; recording time will therefore be documented and considered in sensitivity analyses. Audio recordings will be stored in uncompressed WAV format to preserve signal integrity during feature extraction. All files will be labeled using pseudonymized alphanumeric identifiers. Speaker diarization will identify participant and interviewer segments, followed by manual review. Overlapping or uncertain segments will be excluded, and the original recording will be preserved unchanged. For acoustic and paralinguistic analyses, only participant speech will be retained. The complete interaction will be automatically transcribed and manually reviewed to correct transcription and speaker-attribution errors. Linguistic variables and contextual text embeddings will be extracted from the reviewed participant transcripts, while interviewer turns will be retained as conversational context.

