For each recording, total recording duration, cumulative valid participant-speech duration, silence-to-speech proportion, number of intelligibly transcribed words, and relevant recording incidents will be documented. A minimum of two minutes of cumulative valid participant speech will be required for the primary multimodal analysis. consistent with previous studies using short samples [11,19]. Recordings below this threshold will be considered non-evaluable for that analysis, but the participant will not be excluded from the study.

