**Table 2 pone.0353827.t002:** Study variables recorded in the VOICE-DEP case report form and assessment schedule.

Domain	Description	Assessment visits
Participant identification	Participant category (patient or control), study code, and visit date	V0–V4 in patients; V0 in controls
Sociodemographic and anthropometric baseline variables	Sex, age, marital status, place of residence, birth order in the sibship, height, weight, body mass index, body surface area, educational level, childcare responsibilities, caregiving responsibilities for dependent relatives, religious belief, community religious practice, and social relationships	V0 only
Lifestyle, family history and contextual baseline variables	First-degree family psychiatric history, toxic habits, tobacco, alcohol, cannabis, cocaine, amphetamine and other substance use, physical activity, diet pattern, complementary or alternative treatments and specific prescribed diets, pharmacogenetic or pharmacodynamic isoform information when available, employment status, night work, acute and chronic stressful life events, and current and lifetime traumatic events	V0 only
Clinical baseline variables	Principal diagnosis according to ICD-10 depressive categories, psychiatric comorbidities, medical comorbidities, previous suicidal ideation, previous suicidal behavior, previous self-harm, duration of the current episode, time since initial diagnosis, and number of previous depressive episodes	V0 only
Recording and audio traceability variables	Whether the voice recording was obtained, pseudonymized audio file identifier, presence of recording incidents, and type of incident (patient need, clinical need, technical problem, others)	V0–V4 in patients; V0 in controls
Clinician-rated and self-reported symptom variables	Depressive symptom severity assessed with MADRS, global clinical impression assessed with CGI, and self-reported depressive symptom burden assessed with PHQ-9	V0–V4 in patients; V0 in controls
Pharmacological treatment variables	Pharmacological treatment received, including total daily dose in mg/24h, dosing interval, administration time, and duration of treatment at the recorded dose	V0–V4 in patients
Non-pharmacological treatment and psy-chotherapy variables	Sleep hygiene measures, diet pattern, regular physical activity, discontinuation of toxic habits, psychotherapy attendance, psychotherapy type, and psychotherapy frequency	V0–V4 in patients

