### 3.1. Limitations and methodological considerations

Several limitations and anticipated challenges of the proposed protocol should be acknowledged, particularly those inherent to voice-based clinical studies that seek to balance standardization, ecological validity, and translational feasibility.

Although speech recordings are obtained under controlled hospital conditions, substantial inter-individual variability in speaking style, emotional expressiveness, and engagement during clinical interviews is expected. To balance standardization with clinical realism, a semi-structured, clinician-administered interview protocol is used to elicit naturalistic speech. This improves ecological validity and clinical relevance, but may introduce variability in speech content, duration, and topic coverage, which can in turn affect both acoustic and linguistic measurements.

Longitudinal data collection poses practical challenges. Repeated assessments increase participant burden and may lead to missed visits or incomplete follow-up data. To mitigate this risk, follow-up visits are scheduled within flexible time windows and all procedures are designed to be brief and minimally invasive. Nevertheless, some degree of attrition is anticipated and will be explicitly addressed in the analytical strategy.

The planned sample size remains moderate. While the longitudinal structure provides valuable information on intra-individual vocal trajectories, a moderate sample may limit statistical power, increase uncertainty in performance estimates, constrain the exploration of complex interaction effects, and raise the risk of overfitting, particularly for higher-dimensional or multimodal models.

Technical variability in recording conditions such as background noise or microphone positioning, may influence acoustic measurements. The protocol addresses this by using a standardized recording device and placement, while intentionally avoiding laboratory-grade equipment to maximize clinical applicability. This trade-off prioritizes real-world deployability over maximal signal fidelity and may reduce the signal-to-noise ratio for certain acoustic digital biomarkers.

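### Holding equipment and conditions constant does not stop measured HNR (and, less so, shimmer) from falling when a speaker is quieter, and the plan records no signal-to-noise ratio that would reveal it

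*Protocol article*

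**What the plan says.** Section 2.5 requires a quantity of usable speech: "A minimum of two minutes of cumulative valid participant speech will be required for the primary multimodal analysis". The consequence of failing is tied to that threshold alone: "Recordings below this threshold will be considered non-evaluable for that analysis". The per-recording documentation is also listed: "total recording duration, cumulative valid participant-speech duration, silence-to-speech proportion, number of intelligibly transcribed words, and relevant recording incidents will be documented". Table 2 (section 2.6) adds whether a recording was obtained, the file identifier, and "presence of recording incidents, and type of incident (patient need, clinical need, technical problem, others". None of these items is a noise level or an SNR.

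On the acoustic environment, section 2.5 says "Recordings will be conducted in a quiet hospital room, with minimized background noise", with the microphone at most 20 cm from the mouth. It accepts that the chosen device may make jitter, shimmer, HNR and intensity less precise, and gives this remedy: "This potential variability will be reduced by maintaining the same microphone, configuration, placement, and recording conditions throughout the study". SNR appears once, as a limitation in section 3.1: "This trade-off prioritizes real-world deployability over maximal signal fidelity and may reduce the signal-to-noise ratio for certain acoustic digital biomarkers".

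The Introduction names intensity among the speech characteristics altered in depressive states. Table 3 lists HNR, jitter, shimmer and mean intensity as predefined acoustic variables, and section 2.6 counts the extracted speech variables as primary outcome variables.

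**The concern.** The plan treats the device and room effect as random imprecision. For HNR it can also be a bias that depends on how loudly the person speaks. Room noise adds to the voice's own noise. If the room noise is constant, a quieter speaker has a lower SNR and therefore a lower measured HNR, even when the voice is equally clear. A constant microphone, placement and room fix the noise floor but not the speaker's level, so the stated remedy does not reach this mechanism.

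The plan itself expects loudness to be related to depression. The error could therefore follow group at baseline and severity across V0 to V4, and would not average out. A difference in HNR or shimmer could then be reported, or credited by the SHAP analysis in section 2.7, as a voice-quality marker when it only repeats the intensity difference. Without SNR on record, nobody could tell the two apart.

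**Working it through.** **The plan's own figure.** Section 2.4 gives a detectable d of about 0.70 for 25 patients against 50 controls, two-sided 0.05, 80% power.
- Normal approximation: (1.960 + 0.842) × √(1/25 + 1/50) = 2.802 × 0.2449 = 0.686.
- Noncentral t: 0.695, with power 0.805 at d = 0.70.

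The figure reproduces and serves below only as a yardstick.

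**Model for HNR.** Background noise adds to the voice's own noise:

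measured HNR = −10 log10(10^(−HNR/10) + 10^(−SNR/10)).

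With a fixed noise floor, a speaker who is L dB quieter has SNR − L.

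**Assumed inputs (none is in the protocol).** True HNR 15 dB in both groups, patients 5 dB quieter, between-person SD of HNR 2 to 3 dB, and a range of SNR values for the controls.

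| Controls' SNR (dB) | Patients' SNR (dB) | Measured HNR, controls vs patients (dB) | Spurious gap (dB) | Spurious d (SD 3 to SD 2) |
|---|---|---|---|---|
| 20 | 15 | 13.81 vs 11.99 | 1.8 | 0.61 to 0.91 |
| 25 | 20 | 14.59 vs 13.81 | 0.8 | 0.26 to 0.39 |
| 30 | 25 | 14.86 vs 14.59 | 0.3 | 0.09 to 0.14 |

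First row in full: 10^(−1.5) + 10^(−2) = 0.03162 + 0.01000 = 0.04162, giving 13.81 dB; 0.03162 + 0.03162 = 0.06325, giving 11.99 dB. The gap is 1.82 dB; 1.82/3 = 0.61 and 1.82/2 = 0.91. A 3 dB loudness gap at SNR 20 gives d = 0.31 to 0.47.

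**A second set of assumptions.** True HNR 20 dB, a 6 dB loudness gap, and SNR taken against total voice power:
- SNR 25: gap 2.36 dB. With SD 3, d = 0.79 and the chance of p < 0.05 with 25 vs 50 is 0.89. Over SD 2 to 4, d is 1.18 to 0.59 and that chance is 0.997 to 0.66.
- SNR 30: gap 1.05 dB. With SD 3, d = 0.35 and the chance is 0.29.
- SNR 40: gap 0.13 dB. With SD 3, d = 0.04 and the chance is 0.053, essentially the nominal level.

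The effect is negligible once SNR exceeds the true HNR by roughly 15 to 20 dB.

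**Shimmer and jitter.** The formula covers HNR only. A synthetic voice with fixed properties and added white noise gave:

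| SNR (dB) | HNR (dB) | Shimmer (%) | Jitter (%) |
|---|---|---|---|
| no added noise | 20.6 | 2.96 | 0.344 |
| 30 | 19.9 | 3.03 | 0.357 |
| 20 | 16.8 | 3.59 | 0.360 |
| 10 | 9.5 | 6.20 | 0.382 |

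From no added noise to SNR 20, HNR drops 3.8 dB, shimmer rises by about 21% (3.59/2.96) and jitter by about 5% (0.360/0.344). HNR is the feature at risk, shimmer less so, jitter only slightly.

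**The case against.** The strongest reply is that this is a condensed article, and technical audio checks usually sit in a fuller document. Section 2.3 has recording incidents feed into a data quality assessment, section 2.5 has manual review with uncertain segments removed, and section 2.7 has quality control after every visit. An unlisted quality item would not by itself be a finding. What remains is that the article states both the diagnosis (imprecision) and the remedy (constancy), and that remedy leaves a level-dependent bias in place and undetected.

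The second reply is that the room is to be quiet and the microphone close, both of which raise SNR. This stands, and the effect may be trivial in practice. It does not show that it is trivial, because nothing is measured.

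Third, mean intensity is extracted, the study is an exploratory pilot, and the original recordings are kept. All true, and they limit the damage mainly to attribution between HNR and loudness. But intensity without the noise floor is not SNR, and the audio does not last: section 2.9 has it destroyed by 1 January 2030, and section 3.2 plans to release HNR, jitter and shimmer values without it.

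Fourth, strict remedies can do harm. With fixed noise, SNR is speech level minus a constant, so adjusting for it may remove a genuine effect that travels with loudness. A cutoff drops quieter speakers first: in the 25 vs 20 dB row above, a 25 dB minimum keeps controls and loses patients. This stands and shapes the fix.

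**Conclusion.** The point holds as a possible, unmeasured bias in HNR and, to a lesser degree, shimmer. Constant equipment and conditions cannot remove it, and the documented items cannot reveal it. Under the stated assumptions the spurious d runs from 0.61 to 0.91 at SNR 20 dB, near or above the study's detectable 0.70, down to 0.09 to 0.14 at SNR 30 dB, and it is negligible at higher SNR. These figures rest on an assumed HNR, SNR, loudness gap and SD.

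A reader might infer three stronger things that the protocol does not support:
- That HNR will differ artefactually between the groups. No SNR or loudness gap is given, and a quiet room with a close microphone could make the effect negligible.
- That jitter is equally compromised. It barely moved in the check above.
- That the two-minute rule is wrong, or that low-SNR recordings must be excluded. The rule serves its own purpose, and exclusion could remove quieter patients selectively.

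**What to change.** In section 2.5, add recording SNR to the documented items. Compute it from the preserved original file as participant-speech level against the level in non-speech intervals, and report it by group and visit.

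In section 2.7, add a prespecified sensitivity analysis that gives the group comparison and the mixed-effects results for HNR and shimmer (and jitter) with and without recording SNR as a covariate. State that a result that does not survive adjustment will not be interpreted as a voice-quality marker independent of loudness.

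Do not impose an SNR exclusion in the main analysis. If a cutoff is wanted, confine it to a sensitivity analysis, fix it before group data are seen, and report exclusions by group.

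The cost is a short computation on audio that is kept anyway, one sentence in each section, and one extra analysis. It also covers recordings already made, provided it is run before the audio is destroyed. The drawback is that the adjusted estimate may absorb genuine loudness-linked signal, which is why both estimates should be shown.

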## 1. Introduction

Major depressive disorder (MDD) is one of the leading contributors to global disability, affecting more than 280 million people worldwide and constituting a major public health challenge [1]. Despite decades of research, clinical assessment and monitoring of depression still rely predominantly on structured interviews and rating scales, which are inherently subjective and susceptible to recall bias and inter-rater variability [2,3].

In recent years, the identification of objective, scalable and non-invasive digital biomarkers has become a central goal of precision psychiatry [4]. Among behavioral signals, human speech has emerged as a promising source of information because speech production integrates motor control, cognition, affective regulation and autonomic function [5]. Alterations in prosody, speech rate, pauses, intensity and voice quality have been consistently associated with depressive states [6,7].

Recent advances in artificial intelligence have accelerated research on voice-based depression assessment. Machine learning, natural language processing and large language models have shown promising results using acoustic, paralinguistic and linguistic features extracted from speech recordings [8,9]. In parallel, recent studies have increasingly adopted multimodal approaches integrating audio and text information. Representative studies in the field are summarized in Table 1.

**Table 1 pone.0353827.t001:** Representative state-of-the-art studies in voice-based depression research.

Reference	Design and Dataset	Sample (N)
Jin et al., 2026 [10]	Cross-sectional; MMPsy adolescent dataset (text + audio, PHQ-9).	1275 participants
Li et al., 2025 [11]	Cross-sectional; AVEC2013 and AVEC2014 speech datasets (BDI-II).	84 participants (150 clips)
Xu et al., 2025 [12]	Cross-sectional; CMDC and DAIC-WOZ multimodal datasets (voice + text, PHQ-8).	234 participants
Ali et al., 2025 [13]	Longitudinal; DEW dataset (multimodal speech).	Not reported
Mazur et al., 2025 [14]	Cross-sectional; remote personal devices.	14,898 participants
Zhang et al., 2024 [9]	Cross-sectional; DAIC-WOZ dataset (text + acoustic landmarks).	189 interviews
Ghosh et al., 2024 [15]	Cross-sectional controlled; DAIC-WOZ.	189 participants
Huang et al., 2024 [16]	Cross-sectional controlled; DAIC-WOZ.	189 participants
Sadeghi et al., 2024 [17]	Cross-sectional; E-DAIC dataset (text + facial features, PHQ-8).	275 interviews

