Neurostimulation variables	Receipt of electroconvulsive therapy in the current episode, type of electroconvulsive therapy, and other neurostimulation treatments	V0–V4 in patients

**Table 3 pone.0353827.t003:** Multimodal voice- and speech-derived variables predefined in the VOICE-DEP protocol.

Domain	Variable/ group of variables	Operationalization/ measurement
Acoustic	Pitch	F0 mean, standard deviation and range (Hz).
	Energy/ intensity	Mean and standard deviation (dB).
	MFCCs	Coefficients 1–13 summarized by mean and standard deviation.
	Harmonic-to-noise ratio	dB.
	Jitter	Percentage (%).
	Shimmer	Percentage (%).
	Spectral descriptors	Spectral centroid, roll-off and slope (Hz or normalized units).
	Formants	F1–F3 mean frequency and bandwidth (Hz).
	Spectral/ prosodic entropy	Dimensionless entropy index.
	Embedding-based acoustic features	High-dimensional vector representations derived from pretrained models (e.g., Wav2Vec2, HuBERT).
Paralinguistic	Speech rate/ articulation rate/ pause duration	Words per second and pause duration in seconds.
	Prosodic range	F0 and intensity variability (Hz, dB, or coefficient of variation).
	Pause ratio	Silence-to-speech proportion (0–1 or %).
Linguistic	Sentiment polarity	Continuous score from −1 to +1.
	Negative emotional word ratio	Percentage (%) of negatively valenced words.
	First-person singular pronouns	Percentage (%) or frequency per 100 words.
	Lexical diversity	MTLD, Honor´e and type-token ratio.
	Word count/ mean sentence length	Number of words and words per sentence.
	Lexical sentiment variance	Standard deviation of sentiment scores.
	Lexical coherence/ cohesion	Cosine similarity based on semantic embeddings.
	Contextual text embeddings	High-dimensional representations extracted from a pretrained open-weight language model.

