Psychotic status will be considered as a potential confounder and included as a binary covariate when the sample permits stable estimation. Sensitivity analyses excluding patients with psychotic depression will be performed, while subgroup comparisons will be considered exploratory.

Regularized logistic regression will be the primary classification model, with a linear support vector machine and random forest models used for comparison. Missing data, including their frequency, pattern, and documented reasons, will be reported by variable and visit. Mixed-effects models will include a participant-specific random intercept, time as a fixed effect, and selected time-varying covariates; a random slope for time will be considered if supported by the data. The Benjamini–Hochberg procedure will control the false discovery rate within each feature family, and feature selection and hyperparameter tuning will be performed within each training partition.

Because repeated recordings from the same patient are not independent, all longitudinal analyses, predictive modeling and validation procedures will use participant-level data splitting and account for within subject correlation, in order to preserve the independence of training and test data. Specifically, all recordings from the same participant will be assigned exclusively to either the training or the test partition, in order to reduce optimistic bias due to repeated observations from the same individual and avoid information leakage. In this context, Leave-One-Group-Out cross-validation will be used as an appropriate validation framework for grouped repeated-measures data.

To improve clinical interpretability, feature attribution analyses will be performed using Shapley-based methods, including SHAP values where applicable. These analyses will help identify which acoustic, paralinguistic, and linguistic signals contribute most strongly to model predictions and will support the interpretation of the relative importance of different multimodal domains. No imputation for missing data will be applied. To maximize the data collection, quality control reviews will be conducted after every visit. A flexible time-window for visits and periodic reminder phone calls will be planned to reduce the risk of follow-up losses.

All analyses will be performed using Python v3.x or equivalent validated statistical software. Statistical significance will be considered at a two-sided threshold of p < 0.05.

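### The two-minute speech minimum selects recordings on a quantity tied to the study's own outcome variables, which biases speech-quantity contrasts toward the null in the analyses it governs

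*Protocol article*

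**What the plan says.** Section 2.5 sets the rule: "A minimum of two minutes of cumulative valid participant speech will be required for the primary multimodal analysis". It continues: "Recordings below this threshold will be considered non-evaluable for that analysis, but the participant will not be excluded from the study". The same paragraph has valid speech duration, silence-to-speech proportion, word count and incidents documented for every recording.

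Section 2.6 makes the speech-derived variables the primary outcome variables. Table 3 lists among them word count ("Number of words and words per sentence"), pause ratio ("Silence-to-speech proportion"), pause duration and speech rate. The Introduction states the premise: "Alterations in prosody, speech rate, pauses, intensity and voice quality have been consistently associated with depressive states".

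On missing data, section 2.7 says "No imputation for missing data will be applied" and "Missing data, including their frequency, pattern, and documented reasons, will be reported by variable and visit". It does not define the primary multimodal analysis. The primary objective in section 2.1 is discrimination between patients and healthy controls.

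**The concern.** A recording leaves the primary multimodal analysis when its valid speech time is low. Word count is roughly speech time multiplied by speech rate, and pause ratio has speech in its denominator. The rule therefore selects on something close to the response, and the protocol itself expects that response to differ with depression. Severe and psychotic depression and inpatients are eligible, so sparse speech is foreseeable.

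Selection on a covariate such as MADRS would leave a correctly specified slope unbiased. Selection on the response does not, and analysing only the recordings that remain does not correct it. A mixed model does not repair it either: for a speech-quantity response, whether a value enters the model depends on the value that was left out.

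At stake is whether the main analysis understates the markers that reflect how much a participant speaks, and whether it under-represents the least talkative participants. The article names sensitivity analyses for recording time (section 2.5) and psychotic status (section 2.7), but none for this threshold, and the limitations do not mention it.

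**Working it through.** **Inputs from the article.** Threshold 2 minutes; recording 10–30 minutes (section 2.3), so the threshold is 2/10 = 20% to 2/30 = 6.7% of the recording; 25 patients and 50 controls; two-sided alpha 0.05, power 80%, d = 0.70 (section 2.4). The share of recordings below two minutes and the link between speech time and severity are not given, so they are assumed and varied below.

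**1. The plan's own figure.** Detectable d = (1.960 + 0.842) × √(1/25 + 1/50) = 2.802 × 0.245 = 0.686. With the t distribution it is 0.695, and power at d = 0.70 is 0.805. The stated 0.70 reproduces.

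**2. Patient-control contrast on a speech-quantity marker.** Take controls N(0, 1) and patients N(−0.70, 1), and apply one cut-off to both groups at the quantile that removes the stated share of patients.

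| Patients dropped | Controls dropped | d among those kept |
|---|---|---|
| 0 | 0 | 0.70 |
| 2% | 0.3% | 0.68 |
| 5% | 0.9% | 0.65 |
| 10% | 2.4% | 0.62 |
| 20% | 6.2% | 0.56 |

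The AUC of this single marker falls from 0.69 to 0.66 at 20%.

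**3. Correlation with severity, if the rule extends to it.** Let S be standardized severity and D = ρS + √(1 − ρ²)ε be speech quantity. Drop the lowest share q of D.

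| True ρ | q = 2% | 5% | 10% | 20% |
|---|---|---|---|---|
| −0.30 | −0.28 | −0.27 | −0.26 | −0.23 |
| −0.50 | −0.48 | −0.46 | −0.44 | −0.40 |
| −0.70 | −0.68 | −0.66 | −0.64 | −0.60 |

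The dropped recordings come from more severe cases: mean S is 0.7 to 1.7 SD above average at 2% dropped, and 0.4 to 1.0 SD above at 20%.

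**4. Mixed model.** With 25 patients, 5 visits, a random intercept, time as a fixed effect and a true slope of −0.50, the estimated slope averages −0.45, −0.42 and −0.37 when 5%, 10% and 20% of recordings are dropped.

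**5. Speech time in minutes.** Assume MADRS ~ N(25, SD 9) and log(speech time) = log(median) − b(MADRS − 25)/10 + N(0, SD s), with b = 0.25 or 0.35 (1 − e^−b = 22% or 30% less speech per 10 MADRS points) and s = 0.6 or 0.7. Keep recordings above 2 minutes and compare the slope on MADRS with the full-data slope.

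| Median speech at MADRS 25 | Recordings excluded | Slope kept / true slope |
|---|---|---|
| 3.5 min | about 19–23% | 0.58–0.64 |
| 6 min | about 4–8% | 0.79–0.85 |
| 10 min | 0.6–1.8% | 0.92–0.96 |

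**6. Other features.** Take a feature with true r = −0.40 with severity, ρ = −0.50 and 20% dropped. If it is unrelated to speech quantity given severity, its slope stays at −0.40 and r moves to −0.38. If its residual is positively related to speech quantity, r becomes −0.30. If negatively related, r becomes −0.49. The direction is not fixed.

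**The case against.** Much of the opposing case stands.

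- **Scope.** The rule covers one analysis, and the participant stays in the study. The severity correlations and mixed models are described separately and are not said to be under the threshold. A reader might infer that the rule weakens severity associations in general. The documents do not support that: the term is undefined, and the primary objective points to patient-control discrimination. Even under the rule, attenuation is assured only for markers tied to speech quantity (step 6).
- **Cause.** A reader might also infer that recordings drop out only because the participant said little. Valid speech time also falls through interruptions and technical problems (section 2.3) and through removal of overlapping or uncertain segments (section 2.5). Nor need a short recording be extreme on pause ratio: brief answers in a brief interview can contain few pauses.
- **Size.** If participants typically speak for 10 minutes, the bias is negligible.
- **Attrition.** Section 3.1 says "some degree of attrition is anticipated and will be explicitly addressed in the analytical strategy", and a reader might infer that this promise goes unmet. That is too strong. Section 2.7 plans reporting of missingness, mixed models can use all available visits, and further detail commonly belongs in an analysis plan that is not shown.
- **Purpose.** A minimum duration is a reasonable quality criterion, which the article supports by citation, and classifier results are labelled exploratory.

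What does not yield is narrower. The protocol itself fixes an exclusion that depends on speech quantity and rules out imputation, and it does not say which analyses the exclusion reaches.

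**Conclusion.** The point holds in a limited form. In whatever analysis the threshold governs, contrasts on speech-quantity-linked markers are biased toward the null; for other features the bias may be absent or of either sign.

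The size runs from negligible to substantial. The slope of log speech time keeps between 0.58 and 0.96 of its true value over medians of 3.5 to 10 minutes, and a patient-control d of 0.70 becomes 0.68 to 0.56 when 2% to 20% of patient recordings are dropped. Since 0.70 is about the smallest difference the study can detect with 80% power, the upper part of that range would matter even if only discrimination is affected.

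These figures rest on an assumed speech-time distribution, an assumed link with severity and an unknown share below two minutes. They also treat low speech as the only route below the threshold. The severity-slope figures apply only if the rule reaches those analyses.

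**What to change.** Recruitment is ongoing and analysis is planned for February 2028, so this can still be prespecified.

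1. Define the primary multimodal analysis in section 2.7, and state which analyses the two-minute minimum governs and which it does not.
2. Keep recordings below the threshold for speech-quantity, speech-rate and pause variables. Section 2.5 already documents most of what is needed for every recording.
3. Report the number of non-evaluable recordings by group, visit and MADRS, separating low speech from technical problems or interruption.
4. Add one sensitivity analysis of the primary multimodal analysis without the threshold, with valid speech duration carried as a variable.

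The cost is wording, plus noisier features from short recordings. I would not add inverse-probability weights for evaluability: with 25 patients and possibly few short recordings they would be unstable.
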